### Interventions

A.**No menthol restriction**: Participants randomized to the regulatory scenario with no menthol restriction will continue to receive their usual menthol cigarettes and a menthol-flavored e-cigarette. This was selected as a control condition because it models the current status quo scenario where there is no prohibition of menthol in either product. This design also allows for consistency across conditions since all participants will have access to both cigarettes and e-cigarette products with the primary difference being the flavor of the products. We selected commercially-available pod e-cigarettes in 5% nicotine salt concentration for this study for several reasons. These are the most popular e-cigarettes on the market [37, 38], and they have a nicotine pharmacokinetic profile like that of combustible cigarettes with more favorable subjective ratings than other e-cigarettes [27, 39], which may make them a more acceptable substitute for adults who smoke cigarettes. Additionally, pod e-cigarette devices have design features that enhance ease of use, consistency of experience, and safety for the user. These e-cigarettes are small, do not require knowledge of modifying temperature/voltage controls, and are a closed system, meaning the device and e-liquids are not modifiable by the participant and it does not require refilling e-liquid cartridges.B.**Menthol prohibited in cigarettes**: Participants randomized to the regulatory scenario with menthol flavor prohibited in cigarettes but not e-cigarettes will be switched from their usual menthol cigarettes to replacement non-menthol cigarettes of the same brand (e.g., switching from Newport menthol to Newport non-menthol) and will receive a menthol-flavored e-cigarette. A matched-brand non-menthol cigarette comparison was selected based on real-world evidence from a menthol ban in Canada where it was observed that the tobacco industry encouraged consumers to maintain brand loyalty and switch to their same-brand non-menthol products after the ban [40, 41].C.**Menthol prohibited in cigarettes and e-cigarettes**: Participants randomized to the regulatory scenario with menthol flavor prohibited in cigarettes and e-cigarettes will receive matched-brand non-menthol cigarettes and a tobacco flavored e-cigarette.

### Measurements

#### Primary outcome measure

The primary outcome measure is changes in cigarettes smoked per day. At each assessment, participants will report the total number of cigarettes consumed each day and the total number of times the e-cigarette is used each day using well-validated timeline follow-back (TLFB) interview methods [42]. The primary outcome will examine the average number of cigarettes smoked per day in the past week at visit 0, 2, 4, 6, and 8 to evaluate changes in smoking behavior by regulatory scenario. Additional outcomes will assess the percent days smoke-free and percent days of e-cigarette use during the 8-week period.

#### Secondary outcomes

Secondary outcomes will compare percent days smoke-free measured via TLFB assessments. Additional secondary outcomes include changes in nicotine dependence measured by the PROMIS® measure of cigarette dependence and a corresponding measure of e-cigarette dependence [43–45], and motivation, confidence, and intentions to quit smoking [46] among the regulatory scenarios.

#### Exploratory outcomes

Exploratory outcomes will examine percent days of e-cigarette use during the 8-week period via TLFB, as well as continued product use and quit attempts at the 12-week follow-up. We will explore differences in continued cigarette and e-cigarette use during the follow-up period and reported quit attempts between groups. We will explore differences in e-cigarette use, including flavors used, between groups as measures of acceptability of the product.

### Data collection, monitoring, and statistical plan

#### Data collection and storage

The proposed study will follow HIPAA guidelines for data collection, management, and monitoring to ensure the protection of participant information. Self-report data will be collected via Yale Qualtrics secure online software to ensure standardized assessments. Participant data will be coded by a unique subject identification number that does not contain any personal identifiers and data will be stored on a password-protected study computer. The key that links the participant to their unique subject identification and research records and any other electronic records (e.g., screening information and contact information) will be stored in a locked file on the encrypted study computer. De-identified data will be stored for analysis and will be available for research purposes to qualified individuals within the scientific community by request from the PI or through an NIH-funded repository.

#### Data safety monitoring plan

In addition to the oversight of the Yale Investigational Review Board (IRB), this project will use the existing Yale TCORS Data Safety Monitoring Board (DSMB) to provide the highest protection for study participants. The composition of the DSMB has been constructed following NIH guidelines and includes individuals with complementary expertise in tobacco use and statistics. The purview of the DSMB includes, but is not limited to, the following areas: assessments of data quality and timeliness, participant recruitment, retention, safety and efficacy data, and protocol compliance.

#### Data analysis plan

Data analyses will be conducted under the supervision of the study biostatistician at the end of the trial. No interim analyses are planned. Data on quantitative outcomes will be examined for conformity to the normal distribution, and if an outcome is not normally distributed, we have several options including applying transformations or utilizing alternative methods (e.g., generalized linear mixed models, nonparametric tests). For smoking outcomes that may be best modeled as count data, we can use generalized linear mixed models with Poisson or negative binomial distributions.

The primary analyses will be based on mixed models which use all available data on individuals, are flexible in accounting for the correlation structure among observations on the same individual and provide unbiased and efficient estimates when the data are missing at random. This approach, therefore, helps to avoid imputing missing data. The mixed model allows us to obtain unbiased and efficient estimates of change over time and between group differences. We will also perform sensitivity analyses based on pattern-mixture models to evaluate the robustness of our results to missing data assumptions.

#### Sample size and power calculations

Power was calculated using PASS software based on effect size estimates from pilot data where we detected an average change of 2.2 cigarettes, Cohen’s d = 0.68 [19]. To be sufficiently powered to detect a similar or smaller effect in the proposed study, we need *N* = 40 per group to achieve 80% power at two-sided alpha level of 0.05. Therefore, we will recruit 50 individuals per group for a total of 150 to allow up to 20% attrition and still achieve the specified power and required sample size of 40 per group. Due to our retention efforts, we expect our attrition rate may be even lower, as attrition in the initial study was less than the estimated 20% (i.e., attrition was 13%). For Aim 1, we will have sufficient power to detect a medium-to-large effect size (Cohen’s d = 0.64, Cohen’s f = 0.32). This corresponds to the ability to detect a difference of at least 2 cigarettes per day (SD = 3) or at least a 13% difference in percent days smoke-free (SD = 20%), consistent with effect size estimates from our work and other studies [19, 33]. For Aim 2, data from our initial work indicated differences across racial groups with a large effect size estimate (Cohen’s d = 1.21) [19]. With the proposed sample size, we will have sufficient power to detect a similar or smaller effect in the range of medium-to-large effect sizes (Cohen’s d = 0.64, Cohen’s f = 0.32) with 80% power at two-sided alpha level of 0.05 for the interactions of interest.

#### Analysis plan aim 1

**Examine the impact of prohibiting menthol flavor in cigarettes and e-cigarettes on smoking behavior**. We will use mixed model analyses to evaluate changes in smoking behavior from Phase I (usual menthol cigarettes) to Phase II (assigned regulatory scenarios). Outcomes were selected to inform the impact of these policies on public health including changes in cigarette use, addiction, and appeal/acceptability of the alternative product. The primary outcome will evaluate changes in the number of cigarettes smoked per day during the 8-week period and will examine differences by regulatory scenario. Regulatory scenario (i.e., no menthol restriction, menthol prohibited in cigarettes only, menthol prohibited in cigarettes and e-cigarettes) will be a between-subject factor and time (week 0, 2, 4, 6, 8) will be a within-subject factor. The best-fitting variance-covariance matrix will be selected based on Schwartz Bayesian Criterion (BIC). We hypothesize (1) greater reductions in cigarette use in the context of menthol flavor prohibited in cigarettes vs. no menthol cigarette restrictions and (2) the greatest reductions in cigarettes per day in the scenario where menthol is prohibited in cigarettes but where menthol e-cigarettes remain available to substitute for cigarettes. We will use focused contrasts to compare the average change in cigarette use between groups to evaluate the effect of prohibiting menthol flavor in cigarettes, e-cigarettes, or both products. We will also estimate the average change in each group by 95% confidence intervals. Secondary outcomes will compare percent days smoke-free between regulatory scenarios, as well as changes in nicotine dependence, motivation and confidence quitting smoking, and intentions to quit smoking between groups using the same approach. Exploratory outcomes will compare percent days of e-cigarette use during the 8-week period, rates of continued product use after products are no longer provided, and quit attempts during the follow-up period to evaluate differences by group. We will use 0.05 significance level for the primary analysis of each aim and Bonferroni-Holm correction for multiple secondary and exploratory analyses. Exploratory analyses of sex as a potential predictive and moderating factor will also be performed by including sex as an additional between-subject factor in the models. We do not have *a priori* hypotheses regarding sex effects in this study and will focus on providing sex-specific effect estimates to inform future studies.

#### Analysis plan aim 2

**Investigate whether outcomes differ by race to understand the impact of the menthol policies on Black individuals given high rates of menthol cigarette use in this population**. Consistent with our initial work, we aim to recruit equal numbers of participants who identify as Black vs. non-Black and will stratify randomization by race. This will allow us to evaluate the impact of the various regulatory scenarios separately by race and to understand the potential benefit specifically for Black individuals who smoke, who are disproportionately impacted by the harms of menthol cigarette use. We will examine whether changes in the outcomes differ by race by including race as an additional between-subject factor in the models above. We will test race*regulatory scenario*time interactions to evaluate moderator effects and race*time interactions to evaluate race as a predictor of outcome. Planned post-hoc analyses will evaluate pairwise differences in changes from Phase I to Phase II to compare the magnitude of the effect of the policy scenarios separately by race (e.g., the reduction in cigarette use for Black participants if menthol is prohibited in cigarettes only vs. both cigarettes and e-cigarettes vs. no policy change). If the findings suggest important differences in the magnitude of the effect between Black vs. non-Black individuals, this can also inform future research aimed at examining effects among specific subgroups by race/ethnicity.

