Aim 1 of the study will examine the impact of prohibiting menthol flavor in cigarettes and e-cigarettes on smoking behavior. The primary outcome will evaluate changes in the number of cigarettes smoked per day during the 8-week exposure to the regulatory scenarios. We hypothesize (1) greater reductions in cigarette use in the scenarios prohibiting menthol cigarettes (groups B/C) vs. no menthol restriction (group A) and (2) the greatest reductions in cigarettes per day where menthol is prohibited in cigarettes but where menthol e-cigarettes are available as a substitute (group B) compared with groups A and C. Secondary outcomes will compare percent days smoke-free, changes in nicotine dependence, and motivation, confidence, and intentions to quit smoking across the regulatory scenarios. Exploratory outcomes will examine percent days of e-cigarette use during the 8-week period as well as continued product use and quit attempts at a follow-up visit at week 12. Aim 2 will investigate whether outcomes differ by race to understand the impact of the menthol policies on Black vs. non-Black individuals given high rates of menthol cigarette use among Black adults. This project will provide critical information to understand whether continued availability of menthol (vs. tobacco) flavor in e-cigarettes will lead to greater reductions in cigarette use and complete switching in the context of a policy prohibiting menthol cigarettes. Findings will provide timely and critical evidence to inform regulatory actions regarding menthol flavor in cigarettes and e-cigarettes.

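### The 80% power stated for Aim 1 is that of one two-arm contrast at 0.05; it does not carry over to hypothesis 2 (B better than both A and C) or to Holm-corrected smoke-free days

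*Protocol article*

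**What the plan says.** The protocol article, under *Sample size and power calculations*, sets 40 analysed participants "per group to achieve 80% power at two-sided alpha level of 0.05", and 50 enrolled per group to allow for 20% attrition. It then states: "For Aim 1, we will have sufficient power to detect a medium-to-large effect size". It gives one detectable effect for this, a "medium-to-large effect size (Cohen’s d = 0.64, Cohen’s f = 0.32"). It translates this into the ability to "detect a difference of at least 2 cigarettes per day (SD = 3") or "at least a 13% difference in percent days smoke-free", with an SD of 20%. It does not say which comparison among the three arms the figure belongs to.

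The Background and *Analysis plan aim 1* state two hypotheses for the primary outcome. Hypothesis 1 is a larger reduction in groups B and C than in A. Hypothesis 2 is the largest reduction in B, where menthol e-cigarettes "are available as a substitute (group B) compared with groups A and C". Both are to be examined by focused contrasts in a mixed model.

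*Secondary outcomes* lists percent days smoke-free. *Analysis plan aim 1* sets 0.05 for the primary analysis of each aim and "Bonferroni-Holm correction for multiple secondary and exploratory analyses". The number of tests in that family is not given.

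**The concern.** The power statement is made for Aim 1 as a whole, but a single effect size with f = d/2 describes two groups. Hypothesis 2 involves two contrasts, and showing that both differ is harder than showing one. The two hypotheses also pull on the same quantity, the position of C. If C behaves like A, hypothesis 2 is easier but the pooled contrast of hypothesis 1 is diluted. If C lies between A and B, B minus C is smaller than B minus A.

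For smoke-free days, the detectable difference is computed at a significance level that the plan itself does not grant to a secondary outcome when several are tested.

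The article presents B versus C, menthol against tobacco flavor in e-cigarettes, as its central policy question. If that contrast comes out null, a reader who trusts the Aim 1 power statement may take the result as evidence of no difference from an adequately powered test.

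**Working it through.** **Inputs.** n = 40 per arm, two-sided 0.05, d = 0.64, 2 cigarettes/day with SD 3 (2/3 = 0.667 SD), and 13 points with SD 20 (13/20 = 0.65 SD), all from the sample size section. Hypotheses are from the Background, and the multiplicity rule from *Analysis plan aim 1*. Each analysis is treated as a simple comparison of change between arms.

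**Step 1: the stated figure.** The noncentrality for one two-sample t test is d × √(n/2) = 0.64 × √20 = 2.86 on 78 df. Power is 80.7%, and the smallest d with 80% power is 0.634. Attrition: 50 × 0.80 = 40. The stated figure reproduces. The pair d = 0.64 and f = 0.32 satisfies f = d/2, the two-group relation. A three-group omnibus F test at f = 0.32 with 120 participants would have 88%.

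**Step 2: the hypotheses at 40 per arm.** Hypothesis 2 is read as B−A and B−C both significant at 0.05. Each has standard error √(2/40) = 0.224 SD, and their correlation is 0.5. Joint power was simulated with pooled variance on 117 df. Hypothesis 1 is the contrast (B+C)/2 − A, with variance (1/4 + 1/4 + 1)/n = 1.5/n and standard error √(1.5/40) = 0.194 SD.

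| Benefit over A, in SD (B; C) | B vs C | Hypothesis 2, both | Hypothesis 1, pooled |
|---|---|---|---|
| 0.64; 0 | 81% | 70% | 37% |
| 0.667; 0 | 84% | 75% | 40% |
| 0.64; 0.32 | 29% | 28% | 69% |
| 0.64; 0.64 | 2.5% | 2.5% | 91% |
| 0.96; 0.32 | 81% | 81% | 91% |
| 1.28; 0.64 | 81% | 81% | 99.8% |

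A hand check of hypothesis 1 by the normal approximation: with C = A the pooled effect is 0.32, and 0.32/0.194 = 1.65, which gives about 38%. With B and C both at 0.64, 0.64/0.194 = 3.30, which gives 91%. In the fourth row B and C do not differ, so hypothesis 2 is false there.

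In the fifth row a B−A difference of 0.96 SD is 0.96 × 3 = 2.9 cigarettes/day, against the average pilot change of 2.2 cited in the sample size section.

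**Step 3: smoke-free days.** The noncentrality is 0.65 × √20 = 2.91 on 78 df. The first Holm step tests at 0.05/m.

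| Tests in family, m | Level at first step | Power for 13 points |
|---|---|---|
| 1 | 0.05 | 82% |
| 2 | 0.025 | 73% |
| 4 | 0.0125 | 64% |
| 6 | 0.0083 | 58% |

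The choice m = 6 assumes one test for each of smoke-free days, cigarette dependence, e-cigarette dependence, motivation, confidence and intentions. The full step-down procedure with six tests gives about 58% if the other five effects are null and about 70% if all six have d = 0.65. At the first step with six tests, 80% power needs about 15.9 points.

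**The case against.** The strongest reply is that nothing in the power section is miscalculated. It claims power to detect an effect size, not joint success on every hypothesis, and that claim reproduces. This stands: the fault lies in the reach of the statement, not in its arithmetic.

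A reader might go further and infer that hypothesis 2 has at most 70% power. The documents do not support that. It holds only if 0.64 SD is the largest difference between any two arms, whereas the article speaks of at least 2 cigarettes per day. If B beats each comparator by at least 0.64 SD, 70% is the floor. With C = A and 50 per arm, so no attrition, power at 0.64 SD is about 82%.

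Nor is 37% the power of hypothesis 1. It requires C to do no better than A, which sits badly with a hypothesis that groups B and C both do better.

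Nor is 58% the power for smoke-free days. It assumes six tests and the first Holm step.

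Testing the primary outcome at 0.05 is no error either. The plan sets that level, and requiring both contrasts to succeed needs no further adjustment. An omnibus three-group test would have 84% if one arm differed from the other two by 0.64 SD, but the stated hypotheses are to be examined by contrasts.

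Two further replies carry some weight. The mixed model uses partial data and repeated measures, which may add power. And an article may leave power by contrast to a fuller document. Here, however, the article itself asserts sufficient power for Aim 1 and a detectable smoke-free-days difference, so the point concerns what is stated, not what is left out.

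**Conclusion.** The point holds in a limited form. The 80% is correct for one two-arm contrast at d = 0.64 and 0.05. Hypothesis 2, if it needs both contrasts, has about 70% when B differs from each comparator by 0.64 SD (75% at 2/3 SD) and 28% if C is midway with B−A = 0.64. Among the patterns tabulated at 40 per arm it reaches about 81% only where B beats C by 0.64 and A by clearly more. Pooled hypothesis 1 ranges from 37% to 91% according to where C lies. The 13-point smoke-free-days figure has 82% only without the correction that the plan prescribes; any family of two or more tests brings the first Holm step to 73% or lower.

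These results assume 40 completers per arm, a simple comparison of change, the both-must-be-significant reading of hypothesis 2, and family sizes that the article does not give. Any gain from the mixed model cannot be quantified, because no within-person correlation is stated. They do not show that the trial as a whole is underpowered.

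**What to change.** In *Sample size and power calculations*, state that the 80% applies to one pairwise contrast at d = 0.64 and an unadjusted two-sided 0.05. Add the power for pooled hypothesis 1, for B versus C, and for hypothesis 2 as a joint claim, each under named patterns of means, for example C equal to A and C midway between A and B.

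For smoke-free days, name the number of tests in the Holm family and restate the detectable difference at that level (about 16 points for six tests at the first step), or label the 13 points as unadjusted.

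The change needs no extra participants and no new design. Its cost is that the stated figures become less favourable.

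### The Aim 2 power statement holds for race-by-time, but d = 0.64 does not describe the race-by-scenario-by-time interaction, which has about 29% power at that size and needs about 1.26 SD

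*Protocol article*

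**What the plan says.** In the Protocol article, the section Sample size and power calculations plans to "recruit 50 individuals per group for a total of 150 to allow up to 20% attrition". The power figures therefore rest on 40 evaluable participants in each scenario.

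For Aim 1 it claims "sufficient power to detect a medium-to-large effect size (Cohen’s d = 0.64, Cohen’s f = 0.32") and translates this into "a difference of at least 2 cigarettes per day (SD = 3").

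For Aim 2 it first cites the pilot: "For Aim 2, data from our initial work indicated differences across racial groups with a large effect size estimate", namely d = 1.21. It then describes what can be detected as "similar or smaller effect in the range of medium-to-large effect sizes (Cohen’s d = 0.64, Cohen’s f = 0.32"). The same sentence closes by saying that this applies "with 80% power at two-sided alpha level of 0.05 for the interactions of interest". The d and f are the same pair as in Aim 1, and no translation into cigarettes per day is given.

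Analysis plan aim 2 says which interactions these are. "We will test race*regulatory scenario*time interactions to evaluate moderator effects" is the first. The second is race-by-time, which treats race as a predictor of outcome. Pairwise scenario comparisons within each race are planned as post-hoc analyses. Equal numbers of Black and non-Black participants are intended, and randomization is stratified by race.

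**The concern.** The Aim 2 sentence gives an interaction the same detectable d, at the same power, as a plain comparison of two arms of 40. A race-by-scenario contrast compares two differences across four cells, each half the size of an arm, so its standard error is twice as large. The same d cannot have the same power for both.

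Aim 2 is one of the trial's two aims, and the three-way interaction is the test that answers it. The only meaning the section gives to d = 0.64 is about 2 cigarettes per day. A reader who carries that meaning forward will think the trial can usually detect a racial difference of that size in a policy effect. On that meaning the test would miss it about seven times in ten.

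**Working it through.** **Inputs.** Two-sided alpha 0.05, power 80%, d = 0.64, f = 0.32, 40 evaluable and 50 recruited per scenario, and SD 3 cigarettes per day (Sample size and power calculations). Allocation is 1:1:1 (Randomization). Race is split equally (Analysis plan aim 2). Hence there are 20 evaluable (25 recruited) per race-by-scenario cell, and 60 evaluable per race. Effects are in units of the SD of change. Power is from the noncentral t or F distribution.

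**1. Aim 1 reproduces.** SE = sqrt(2/40) = 0.224. At d = 0.64, power is 80.7%, and the d detectable with 80% power is 0.634. In raw units, 0.64 x 3 = 1.92, the section's figure of about 2 cigarettes per day.

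**2. Race-by-time, 60 vs 60.** SE = sqrt(2/60) = 0.183. Power at d = 0.64 is 93.5%, and the detectable d is 0.52. The claim holds with room to spare.

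**3. Race-by-scenario-by-time, with d as a difference of differences.** For two scenarios, the contrast is (Black, B − A) − (non-Black, B − A), and SE = sqrt(4/20) = 0.447. Then 0.64/0.447 = 1.43.

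| Contrast | Power at 0.64 SD | SD needed for 80% |
|---|---|---|
| Pairwise, 20 per cell | 29% | 1.26 |
| Pairwise, 25 per cell (no attrition) | 36% | 1.13 |
| Race by (B/C vs A), 20 per cell, SE = sqrt(2 x (1/20 + 1/40)) = 0.387 | 37% | 1.09 |
| 2-df test, range of 0.64 SD across scenarios, 20 per cell | 23–29%, by pattern | 1.22–1.41 (range) |

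At SD 3, 1.26 SD is 3.8 cigarettes per day and 1.09 SD is 3.3.

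**4. Race-by-scenario-by-time, with f = 0.32 as the interaction effect size.** The noncentrality is f² x N.
- 2x2 layout (two scenarios), N = 80, 1 df: 0.1024 x 80 = 8.19, power 80.7%.
- 2x3 layout, N = 120, 2 df: 0.1024 x 120 = 12.29, power 88.2%.

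So the stated 80% can be recovered. In a 2x2 layout, however, a difference of differences C (in SD units) puts an interaction effect of plus or minus C/4 in each cell, so f = C/4 and C = 4 x 0.32 = 1.28 SD. As a check, 1.28/0.447 = 2.86, and 2.86² is again about 8.19. The conversion d = 2f, which gives 0.64, is for a comparison of two groups.

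**5. Within-race pairwise comparisons, 20 vs 20.** SE = sqrt(2/20) = 0.316. Power at 0.64 is 51%, and the detectable d is 0.91 (2.7 cigarettes per day at SD 3).

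**6. The pilot figure.** If d = 1.21 were a three-way difference of differences, power would be about 76–77% with 20 per cell, and about 80% at the pilot's 13% attrition (about 21.75 per cell). The article describes the pilot as a within-person switch with larger reductions among Black participants. That points to a race-by-time quantity, which does not tell us the size of a race-by-scenario effect.

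**The case against.** The strongest reply is that nothing has been miscalculated. Cohen's f is a usual way to express an interaction in a factorial design, and step 4 recovers 80% or more from the article's own f = 0.32. The Aim 2 sentence never says that d = 0.64 means 2 cigarettes per day; that translation stands only in the Aim 1 sentence. This much stands: the 29% depends on carrying the Aim 1 meaning of d into Aim 2. It does not rescue the text. If f = 0.32 is right for the three-way interaction, the d printed beside it is half the effect that f implies; if d = 0.64 is right, the 80% is not.

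A reader might also infer that the power claim is wrong for every race interaction. It is not: race-by-time is one of the two named interactions and is more than adequately powered at d = 0.64. Removing the claim altogether would delete a true statement.

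A reader might further infer that a non-significant three-way test will be reported as equal policy effects by race. No section says so. Analysis plan aim 2 intends to compare the magnitude of effects separately by race and to use important differences to inform later research.

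The pilot d = 1.21 carries little weight either way. Its power as a three-way effect moves to about 80% at the pilot's attrition, and its exact definition lies in a cited study that is not at hand.

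**Conclusion.** The concern holds for the three-way interaction only. The article's d = 0.64 and f = 0.32 cannot both describe a race-by-scenario interaction. On the one meaning the article gives to d, power is about 29%, and 80% power needs a pairwise difference of differences of about 1.26 SD, or 3.8 cigarettes per day, roughly twice the printed d. The Aim 1 calculation and the race-by-time part of Aim 2 stand.

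These figures assume that SD 3 is the SD of change, that the races split equally within each scenario, that attrition is even at 20%, and that repeated measures add no precision beyond what the Aim 1 figure implies. With no attrition at all, the three-way power is still only about 36% at 0.64 SD, so the conclusion does not depend on the attrition allowance.

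**What to change.** In Sample size and power calculations, replace the single Aim 2 statement with one figure per effect, each at 80% power, two-sided alpha 0.05 and 40 completers per scenario:
- race-by-time: keep the claim at d = 0.64 (power about 94%; detectable d about 0.52);
- race-by-scenario-by-time, pairwise: a difference of differences of about 1.26 SD (3.8 cigarettes per day at SD 3);
- race by (B/C vs A): about 1.09 SD;
- planned pairwise comparisons within a race (20 vs 20): about 0.91 SD.

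If f = 0.32 is kept for the three-way interaction, say that it is the interaction f and that in a 2x2 layout it means about 1.28 SD; do not pair it with d = 0.64. State the assumptions on race split, attrition and SD alongside.

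In Analysis plan aim 2, add that the three-way interaction will be reported as an estimate with a 95% confidence interval, so that its precision is visible whatever the p-value.

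The cost is a text change. It needs no extra participants and no change to the design or the tests. The only downside is a less favourable stated figure for the three-way interaction.
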